#### Step 4: Qualitative Interviews

Patient interviews will occur within 1 month after study completion (early withdrawal included), and PCP interviews within 1 month after the last patient’s last visit at each site.

These interviews explore different dimensions of feasibility and usability: perceived relevance and acceptability of the intervention, perceived impact on workloads and workflow, quality and timing of information, interprofessional collaboration, and ethical and data security concerns (Multimedia Appendix 5).

### Outcomes

#### Overview

In the ADER-F study, feasibility refers to the extent to which the intervention can be delivered as intended in routine primary care; it is assessed primarily through the proportion of patients with complete use of Lianeli (primary outcome) and through objective CDSS use and data quality metrics (Table 2). Acceptability refers to the extent to which patients and PCPs consider the intervention appropriate, satisfactory, and usable; it is assessed through the GUIDES-based surveys, the F-SUS usability score, and the qualitative interviews.

#### Primary Outcome

The primary outcome is the proportion of included patients for whom the Lianeli CDSS is used completely. Complete use is defined as meeting all 3 of the following criteria: the patient validates completion of the Lianeli self-administered health questionnaire (criterion 1), the GP checks data quality and validates the patient’s responses (criterion 2), and the dedicated screening consultation is conducted within 60 days after the inclusion consultation (criterion 3). This outcome is binary at the patient level (complete vs incomplete use).

#### Secondary Outcomes

Secondary outcomes are grouped according to study objectives (Table 2).

**Table 2 table2:** Study objectives (SOs) and secondary outcomes: data sources, timing of measurement, and planned analyses.

SOs and secondary outcomes		Data source	Timing of measurement	Planned analysis
**SO1: quantitative feasibility criteria**				
	Percentage of Lianeli health questionnaires started and completed, percentage validated by GPs^a^, number of dedicated consultations, missing data rates before vs after GP review of the health questionnaire, percentage of documented previous screening tests, and patient error rate regarding past examinations	Lianeli CDSS^b^ (automatically recorded metadata)	Continuously recorded from visit 1 to visit 2 (day 1 to day 60)	Descriptive statistics
	GUIDES^c^ patient survey (22 items, including the F-SUS^d^; Multimedia Appendix 3)	eCRF^e^ or paper-based survey, with the help of research assistants if needed	After visit 2, no later than 90 days after inclusion	Descriptive statistics
	GUIDES PCP^f^ survey (22 items, including the F-SUS) (Multimedia Appendix 4)	eCRF or paper-based survey	At the end of the inclusion period	Descriptive statistics
**SO1: qualitative feasibility criteria**				
GUIDES-related interview canvas (Multimedia Appendix 5)		Semistructured interviews	Patients: within 1 month after study completion; PCPs: within 1 month after the last patient’s last visit at each site	Thematic analysis with deductive (GUIDES domains) and inductive coding; NVivo software
**SO2: organizational adjustment and interprofessional collaboration**				
How centers adapt their organization to implement the Lianeli-based intervention (integration into preventive programs and workflows; patterns of interprofessional collaboration		Semistructured interviews	Patients: within 1 month after study completion; PCPs: within 1 month after the last patient’s last visit at each site	Descriptive qualitative synthesis; organizational model derived from qualitative findings
**SO3: explanatory variables for feasibility**				
	Interprofessional use of Lianeli, defined as the involvement of ≥2 health professionals (including the GP) working with the patient during ADER-F	eCRF by research assistants	Documented during the intervention period (day 1 to day 60)	Exploratory regression model on the primary outcome
	Patient health literacy (HLS-EU16^g^, French version; range 0-16; inadequate ≤8, problematic >8 and ≤12, adequate >12)	eCRF or paper-based survey, with the help of research assistants if needed	At inclusion (visit 1)	Descriptive statistics
	Social deprivation (EPICES^h^ score; range 0-100; higher=more deprived; threshold of 30.2 commonly used)	eCRF or paper-based survey, with the help of research assistants if needed	At inclusion (visit 1)	Descriptive statistics

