### Setting

The study will be conducted in 17 primary care centers (participating sites) involving 21 GPs in the Auvergne-Rhône-Alpes region of France. Participating sites will include solo GP practices, one community health care center, and multiprofessional group practices. They may involve other PCPs in the delivery of the intervention (team-based practices), depending on the local organization, as long as a GP conducts both the inclusion and dedicated screening consultations. Before patient recruitment, all participating GPs will receive a standardized online training session on the use of the Lianeli CDSS and on the study procedures, delivered by the research team. There will be no restriction on concomitant care during the study.

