**Other PCPs**			
	Inclusion	Health professionals (eg, nurses and medical assistants) working in participating sites	

^a^GP: general practitioner.

^b^PCP: primary care professional.

^c^ADER-F: Aide aux Dépistages Recommandés-Faisabilité.

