### Statistical Analysis

A data monitoring committee will validate, before statistical analyses, the patient sample to be analyzed, in accordance with the protocol. No interim analyses have been planned. The primary analysis population will be the intention-to-treat population, defined as all included patients regardless of eligibility deviations or level of participation in the intervention. Patients who withdraw or are lost to follow-up will not be replaced.

Quantitative variables will be summarized using standard descriptive statistics: number of observations, number of missing values, mean, SD, median, IQR, minimum, and maximum. When relevant, quantitative variables may be categorized using the median or thresholds based on the literature. Categorical variables will be described using frequencies and percentages (with missing values reported but excluded from denominators).

The proportion of patients with complete use of Lianeli will be estimated with its 95% CI and compared with a prespecified threshold of 70% using a 2-sided exact binomial test. A proportion statistically significantly greater than or equal to 70% will be considered evidence of feasibility. The primary outcome will be evaluated at the end of the study. Secondary quantitative outcomes (Lianeli metadata, questionnaire scores, and screening participation proxies) will be analyzed descriptively. Exploratory analyses will examine associations between the primary outcome and selected determinants of Lianeli use. Given the exploratory nature and the limited sample size of this feasibility study, the variables included in the regression models were prespecified based on clinical and methodological relevance: interprofessional use of Lianeli, health literacy (European Health Literacy Survey Questionnaire-16 [HLS-EU16] score) [27], and social deprivation (Evaluation of Precarity and Inequalities in Health Examination Centres [EPICES] score) [28]. Associations will be described using regression models and reported as effect estimates with their 95% CIs. These analyses will be considered exploratory and hypothesis-generating.

Missing data will be considered informative in this feasibility study. They will be described explicitly and taken into account in the analysis of outcomes, but no imputation or correction methods will be applied.

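### The SO3 regression names no practice-type term although the chance of interprofessional use depends on how a site is organized, so its coefficient can be confounded by practice type

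*Protocol article*

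**What the plan says.** Table 2 (SO3) defines the exposure patient by patient as "Interprofessional use of Lianeli, defined as the involvement of ≥2 health professionals (including the GP) working with the patient during ADER-F".

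Setting describes a mix of organizations: "Participating sites will include solo GP practices, one community health care center, and multiprofessional group practices". It continues: "They may involve other PCPs in the delivery of the intervention (team-based practices), depending on the local organization". Table 1 counts as other PCPs "Health professionals (eg, nurses and medical assistants) working in participating sites".

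Statistical Analysis fixes the covariate list: "the variables included in the regression models were prespecified based on clinical and methodological relevance: interprofessional use of Lianeli, health literacy", followed by social deprivation (EPICES score). No practice-type, site or GP term is named. The same section says of these models: "These analyses will be considered exploratory and hypothesis-generating".

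The article gives neither the number of solo practices, nor how often they work with a second professional, nor the completion expected by practice type.

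**The concern.** A patient can be exposed only if the site has a second professional to involve. Setting makes this a matter of local organization, and its parenthesis links such involvement to team-based practices. Opportunity for exposure is therefore largely a site characteristic. The two named adjustment variables describe the patient and do not capture it.

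The outcome may also vary by site for reasons unrelated to a second professional. Complete use requires that the GP validates the questionnaire and that "the dedicated screening consultation is conducted within 60 days after the inclusion consultation (criterion 3"). Both plausibly depend on appointment supply and administrative support. If completion differs between solo and team practices on such grounds, a model without practice type assigns part of that difference to interprofessional use.

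At stake is the reading of one secondary result. The Textbox of key characteristics calls it an effect on the primary outcome, and Implications speaks of how collaboration influences feasibility. A reader could take a difference between kinds of practice for a benefit, or a harm, of involving a second professional.

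**Working it through.** **The plan's own figures.** The article gives no sample-size or precision figure for SO3. Its figures concern the primary outcome and reproduce: the largest SE at n = 210 is √(0.25/210) = 3.45%, below the stated 4%. They neither support nor weaken this point.

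**Inputs for the illustration.** From the article: 21 GPs with about 10 patients each, 210 in total. Assumed, because the article does not say: 9 solo GPs (90 patients) and 12 team GPs (120 patients); 50% exposure in team practices; no exposure in solo practices; completion 70% solo and 80% team; no effect of interprofessional use within either type (true OR 1).

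**Expected unadjusted odds ratio.**

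- Exposed: 120 × 0.5 = 60 patients, all from team practices, 60 × 0.80 = 48 completing (80%).
- Unexposed: 90 solo + 60 team = 150 patients, 90 × 0.70 + 60 × 0.80 = 63 + 48 = 111 completing (74%).
- OR = (48/12) / (111/39) = 4.00 / 2.85 = 1.41.

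**Varying the assumptions, with everything else as above.**

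| Change | Exposed | Unexposed | OR |
|---|---|---|---|
| Solo 80%, team 70% | 42/60 = 70% | 114/150 = 76% | 0.74 |
| 20% of solo patients exposed | 60.6/78 = 77.7% | 98.4/132 = 74.5% | 1.19 |
| 50% of solo patients exposed, as in teams | 79.5/105 = 75.7% | 79.5/105 = 75.7% | 1.00 |
| Completion 75% in both types | 45/60 = 75% | 112.5/150 = 75% | 1.00 |

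**Wider range.** With a solo share of 20–60%, team exposure of 50–80% and a 10-point completion gap (70% vs 80%), the same formula gives 1.22–1.62 when teams complete more and 0.63–0.85 when they complete less, if solo practices are never exposed. If 20% of solo patients are exposed, the ranges are 1.12–1.38 and 0.73–0.91.

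**How often this would look like a finding.** Logistic regression was simulated under the first scenario, 2,000 runs, patients treated as independent. Without practice type the 95% CI excluded 1 in about 13% of runs. With practice type in the model the estimate centred on 1 and this happened in about 4–6% of runs. With 20% of solo patients exposed, the unadjusted rate was about 7%.

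**Cost of the fix in precision.** In the first scenario the SE of the unadjusted log OR is √(1/48 + 1/12 + 1/111 + 1/39) = 0.373. Using team practices only (48/60 vs 48/60) it is √(2 × (1/48 + 1/12)) = 0.456. The ratio is 0.456/0.373 = 1.22, so the CI is about 22% wider on the log scale.

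**The case against.** Several objections carry weight.

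- *Solo practices may have a second professional.* A reader might infer that solo-practice patients are always unexposed. The article does not say so. A solo GP may work with a nurse or medical assistant, and the sentence on involving other PCPs has all participating sites as its subject. This stands, and with 20% exposure in solo practices the example falls from 1.41 to 1.19.
- *Completion may not differ by practice type.* The article gives no evidence that it does. Without a difference there is no bias, and the direction of any bias is unknown. This stands, so the coefficient can be confounded; it has not been shown to be.
- *Little depends on the coefficient.* A reader might infer that the SO3 estimate will determine the organizational model. Table 2 (SO2) derives that model from qualitative findings, Qualitative Analysis adds triangulation across centers, and Statistical Analysis speaks of associations without a decision rule. This stands and limits the importance of the point. An exploratory label does not remove bias from an estimate, however.
- *The full model may be in a document not shown.* This is true of the regression type and of GP or site effects. The explanatory variables, however, are stated here as prespecified, so the list can be commented on as it is.
- *A solo/team indicator is not a complete remedy.* It leaves differences among team sites uncontrolled. In a simulation with assumed GP-level variation (SD 0.9 on the logit scale) and exposure strongly clustered by GP, the model adjusted for practice type still excluded 1 in about 11% of runs. This stands as a limit of the fix.

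**Conclusion.** The point holds in conditional form. The article makes opportunity for interprofessional use depend on site organization, mixes solo and multiprofessional sites, and names SO3 regression variables that include nothing about the site. If solo practices involve a second professional less often and also complete more or less often for other reasons, the coefficient is biased by practice type.

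Under the assumptions shown, the spurious odds ratio is about 1.4 in the worked example. Across the ranges tried it lies between 1.12 and 1.62, or between 0.63 and 0.91 if team practices complete less. It is 1.00 if either condition fails. Every input beyond 21 GPs and 210 patients is an assumption.

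The consequence is confined to one exploratory estimate. The comparison of the completion rate with 70% is unaffected. Two other issues remain: clustering by GP, and the recording of exposure over the window that also defines the outcome ("Documented during the intervention period (day 1 to day 60").

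**What to change.** In Statistical Analysis, add practice type (solo vs team-based, the latter covering the community health care center and multiprofessional groups) to the exploratory SO3 model. Alternatively, estimate the association among patients of team-based sites only and describe solo practices separately. The two give nearly the same estimate when solo-practice patients are almost all unexposed. Either way, state that the estimate applies where a second professional is available.

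This takes a sentence or two and no new patient-level data, since practice type should be known for the 17 sites. The price is a wider CI, about 22% on the log scale in the worked example, because team-based sites then supply most or all of the contrast. The change addresses neither GP-level clustering nor the shared exposure and outcome window; those need their own treatment or a stated caveat.

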**SO4 and SO5: exploratory signals related to cancer screening participation**				
Among patients eligible for at least 1 organized cancer screening (breast, colorectal, or cervical cancer) who are overdue or have never been screened: proportion attending the dedicated screening consultation within 60 d of inclusion; the same proportion is described among patients eligible for opportunistic cancer screenings		Lianeli CDSS (automatically recorded metadata)	Within 60 days of inclusion	Descriptive statistics (hypothesis-generating)

^a^GP: general practitioner.

^b^CDSS: clinical decision support system.

^c^GUIDES: Guideline Implementation with Decision Support.

^d^F-SUS: French version of the System Usability Scale.

^e^eCRF: electronic case report form.

^f^PCP: primary care professional.

^g^HLS-EU16: European Health Literacy Survey Questionnaire-16.

^h^EPICES: Evaluation of Precarity and Inequalities in Health Examination Centres [Evaluation de la Précarité et des Inégalités de santé dans les Centres d'Examens de Santé].

### Sample Size

As a feasibility study, ADER-F is not designed to detect clinical effects on practice or patient outcomes but to estimate feasibility and acceptability parameters. No formal hypothesis-testing power calculation was performed. Instead, a minimum sample size of 210 patients (approximately 10 patients per GP, across 21 GPs) was chosen to allow precise estimation of the primary feasibility outcome.

A sample size of 210 patients ensures that the SE of the estimated proportion of complete Lianeli use remains below 4%, irrespective of the observed rate. Consequently, observing a complete use rate of at least 77% will allow us to conclude that the true participation rate exceeds 70% (with a 2-sided type I error of 5%).

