**Planned sample size**
21 GPs and at least 210 patients (≈10 patients per GP)

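### The SE bound, the 77% rule and the exact binomial test assume independent patients; with about 10 patients sharing each GP, the stated precision and error rate are not ensured

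*Protocol article*

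**What the plan says.** Sample Size sets "a minimum sample size of 210 patients", described as "approximately 10 patients per GP, across 21 GPs". It claims that this number "ensures that the SE of the estimated proportion of complete Lianeli use remains below 4%, irrespective of the observed rate". From that it concludes that "observing a complete use rate of at least 77% will allow us to conclude that the true participation rate exceeds 70" per cent, at a two-sided error of 5%.

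Statistical Analysis fixes the primary test: the proportion is given with its 95% CI and "compared with a prespecified threshold of 70% using a 2-sided exact binomial test". Feasibility is accepted when the proportion is significantly above that value.

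Primary Outcome defines complete use, patient by patient, through three criteria: the patient completes the questionnaire, the GP checks and validates the answers, and the dedicated consultation takes place within 60 days. Setting adds: "The study will be conducted in 17 primary care centers (participating sites) involving 21 GPs", with local organization differing between sites and a GP holding both consultations.

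The article mentions no ICC, design effect, cluster-adjusted interval, or GP or site effect.

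**The concern.** An exact binomial test and the SE formula behind the 4% bound are valid for independent patients. Here patients come in groups of about 10 under the same GP. The second criterion is an act of that GP, and the third needs the GP to hold a consultation in time. A GP who falls behind with validation or scheduling would make several patients fail together, and a well-organized GP would make them succeed together. Positive correlation within GPs makes the true variance larger than the binomial variance.

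The consequence runs in the optimistic direction: the interval is too narrow and a rate that is truly 70% is declared feasible more often than planned. The article uses this conclusion to decide whether a randomized trial can be justified (Implications; Conclusions). This is not detail left to an analysis plan, because the article itself commits to the SE guarantee, the numerical threshold and the named test.

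**Working it through.** **Inputs from the article:** n = 210, 21 GPs, m = 10 patients per GP, null value 0.70, two-sided 5%, exact binomial test.

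**Assumed:** the ICC, which the article does not give; values from 0 to 0.20 are shown. GP sizes are taken as equal.

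**1. The article's own figures, under independence**

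- Worst-case SE = √(0.25/210) = 3.45%. At p = 0.70, SE = √(0.21/210) = 3.16%. The 4% bound holds.
- Exact test of 0.70: 160/210 (76.2%) gives p = 0.0504; 161/210 (76.7%) gives p = 0.035. The smallest successful count is 161, which rounds to 77%.
- Upper-tail probability at a true rate of 70%: P(X ≥ 161) = 1.9%.

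The figures reproduce without any design effect, so none was included.

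**2. SE with clustering**

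Design effect DE = 1 + (m − 1) × ICC = 1 + 9 × ICC. Worst-case SE = √(0.25 × DE/210).

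Break-even for 4%: DE = 0.04² × 210/0.25 = 1.344, so ICC = 0.344/9 = 0.038. At p = 0.70 the break-even is higher: DE = 0.04² × 210/0.21 = 1.60, so ICC = 0.60/9 = 0.067.

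**3. False declaration of feasibility**

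Only rejection in the upper tail can declare feasibility, so the nominal rate to compare with is 2.5%. The total count was modelled as the sum of 21 beta-binomial counts of size 10 with mean 0.70 and the assumed ICC. The planned test succeeds at X ≥ 161. Read literally, the 77% rule needs X ≥ 162, because 161/210 is 76.7%; both are shown.

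| Assumed ICC | DE | Worst-case SE | P(X ≥ 161) | P(X ≥ 162) |
|---|---|---|---|---|
| 0 | 1.00 | 3.45% | 1.9% | 1.3% |
| 0.02 | 1.18 | 3.75% | 2.8% | 2.0% |
| 0.03 | 1.27 | 3.9% | 3.3% | 2.4% |
| 0.05 | 1.45 | 4.15% | 4.3% | 3.2% |
| 0.10 | 1.90 | 4.76% | 6.7% | 5.3% |
| 0.20 | 2.80 | 5.77% | 11.0% | 9.3% |

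**4. Observed rate needed with an analysis that allows for clustering**

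Take a logit-scale interval with t on 20 df (2.086) and the design effect as variance. Feasibility requires logit(p) − 2.086 × √(DE/(210 p(1 − p))) > logit(0.70) = 0.847.

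- ICC 0.05, p = 0.780: 1.266 − 2.086 × √(1.45/36.04) = 1.266 − 0.418 = 0.847. The threshold is about 78.0%.
- ICC 0.10, p = 0.792: 1.337 − 2.086 × √(1.90/34.59) = 1.337 − 0.489 = 0.848. The threshold is about 79.2%.

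**5. Does the replacement control the error?**

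In simulation at a true rate of 70%, the logit interval with cluster-robust variance by GP and t on 20 df had an upper-tail error of 2.3% to 2.4% over ICC 0 to 0.20.

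**The case against.** **The ICC is unknown and may be small.** All GPs receive the same training (Setting), research assistants telephone every patient and help with connection (Data Collection and Management), and GPs are compensated for the consultation (Ethical Considerations). The first criterion is the patient's own act, and the third also needs the patient to attend. This stands in part. It makes an ICC of 0.20 speculative, and below about 0.02 to 0.03 the 4% bound and the written 77% rule survive approximately. It does not show that the ICC is negligible, and the article claims a guarantee.

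**The two-sided rejection rates look far worse.** A reader might quote the true two-sided size of the planned test, 9.1% at ICC 0.05 and 14.0% at ICC 0.10, as the rate of wrong feasibility claims. Those figures include rejections below 70%, which can never declare feasibility. The upper-tail rates are the relevant ones.

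**The regression for secondary objective 3.** A reader might extend the criticism to it. The article says only that "Associations will be described using regression models and reported as effect estimates with their 95% CIs", labels the models exploratory, and fixes no independence-based form. The covariance structure can be settled in an analysis plan, so there is no finding there.

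**This is a feasibility study read together with qualitative results.** True, and it softens the consequences, but Statistical Analysis ties evidence of feasibility to this one test.

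**Conclusion.** The concern holds in conditional form. The arithmetic in Sample Size is correct for 210 independent patients; the unsupported step is to present it as guaranteed for patients grouped under 21 GPs. The worst-case SE exceeds 4% once the ICC is above 0.038. False feasibility under the planned test exceeds its nominal 2.5% by an ICC of 0.02, and is about 1.7 times nominal at 0.05 (4.3/2.5) and 2.7 times at 0.10 (6.7/2.5).

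It would go too far to say that the 4% bound and the 77% threshold are simply wrong: that depends on an ICC which the article does not give. The results assume equal GP sizes and a beta-binomial model. Unequal recruitment or further correlation within sites would increase the inflation.

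**What to change.** 1. In Statistical Analysis, make the primary analysis a 95% CI that allows for clustering by GP, for example on the logit scale with cluster-robust variance and t on 20 df. Declare feasibility if its lower limit exceeds 70%. Keep the exact binomial test as a sensitivity analysis.
2. In Sample Size, state that the SE below 4% and the 77% threshold hold under independence. Add the worst-case SE for assumed ICCs (4.2% at 0.05, 4.8% at 0.10) and illustrative thresholds from the same method as the analysis (about 78.0% and 79.2%). Say that the actual cut-off depends on the observed spread between GPs, so no single percentage is the decision rule.

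**Cost:** a change of wording and a few lines of code, to be fixed before the data are analyzed; no interim analysis is planned, so this remains possible. Recruitment and data collection do not change and no extra patients are required. What is given up is precision: the observed rate needed is somewhat higher. Restoring the planned precision at 10 patients per GP would take 210 × 1.45 ≈ 305 patients at ICC 0.05 or 210 × 1.90 = 399 at ICC 0.10. That is not proposed here, but the article should not imply that the precision is already secured.
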